### Predictor assessment

All Pre-ECPR score variables were prospectively collected in the Prague OHCA trial, but none was used for decision making regarding ECPR during the study. Age, initial rhythm, no-flow time, and total cardiac arrest time were recorded in the trial's Case Report Form. During patient evaluation in the catheterization laboratory, the following variables were also retrieved: signs of life (spontaneous movements or breathing efforts), pupil size by best visual estimate, end-tidal CO_2_, rSO_2_ using INVOS monitoring, and arterial pH.

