**Entry criteria for enrollment into the Prague OHCA trial**	
Age ≥18 and ≤65 years^a^	OHCA of presumed non-cardiac cause
Witnessed OHCA of presumed cardiac cause	Unwitnessed collapse
Minimum of 5 min of ACLS performed by the EMS team without sustained ROSC	Suspected or confirmed pregnancy
Unconsciousness^b^	ROSC within 5 min of ACLS performed by EMS team
ECLS team and ICU bed capacity in cardiac center available	Conscious patient
	Known bleeding diathesis or suspected/confirmed acute or recent intracranial bleeding
	Suspected or confirmed acute stroke
	Known severe chronic organ dysfunction or other limitations in therapy
	“Do not resuscitate” order or other circumstances making 180-day survival unlikely
	Known pre-arrest cerebral performance category (CPC) ≥ 3

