**Criteria for initiation of ECLS in the invasive strategy group of the Prague OHCA trial**	
No return of spontaneous circulation or return of spontaneous circulation with ongoing shock (defined as sustained hypotension below 90 mmHg of systolic pressure or need for moderate to high doses of vasopressors)	Signs of death or irreversible organ damage
Admission to cathlab not later than 60 min after the collapse/initial call to emergency medical service^c^	Known bleeding diathesis
Consensus of cardiac center team members on extracorporeal life support initiation	Inadequate arterial and/or venous access for femoro-femoral cannulation

Abbreviations: ACLS: advanced cardiac life support; CPC, cerebral performance category; ECLS, extracorporeal life support; EMS, emergency medical services; ICU, intensive care unit; OHCA, out-of hospital cardiac arrest; ROSC, return of spontaneous circulation.

a Age was estimated at the scene of cardiac arrest; patients later found to be older than 65 years were retained in the study.

b Defined as no response to verbal or painful stimuli during ACLS.

c If collapse time was not exactly known, initial call to emergency medical service was considered.

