### Statistical analysis

Model performance will be evaluated in line with established methodological frameworks for external validation of prediction models by Debray et al.^14^

The relatedness of the development and validation cohorts will be evaluated by comparing predictor and outcome frequencies between cohorts, using percentages for categorical variables and means with standard deviations or medians and interquartile ranges for continuous variables, as appropriate. Formal comparisons will be conducted using Pearson’s chi-square test for categorical variables and Welch’s *t*-test or the Mann–Whitney *U* test for continuous variables, depending on data distribution. In addition, c-statistics (AUCs) from logistic regression models predicting cohort membership will be calculated, where a high c-statistic indicates substantial differences between cohorts and a low c-statistic suggests strong similarity. Differences in the distribution of predicted probabilities between cohorts will also be assessed, visualized using box- and scatterplots, and formally tested using Welch’s *t*-test.

Assessment of prediction model performance on the validation cohort will be performed through calibration, discrimination, risk stratification, and model fit statistics. Calibration will be evaluated using calibration-in-the-large, calibration slope, and calibration plots. Calibration-in-the-large assesses whether the predicted probabilities on average are too low, too high, or appropriate. The calibration slope evaluates underfitting or overfitting, that is, whether the predicted probabilities are too close to the mean (underfitting) or too extreme (overfitting), or whether they are adequate. Calibration plots provide a visual presentation of the agreement between observed and predicted event rates. Discrimination ability will be quantified using the ROC AUC and Tjur's discrimination index for the validation cohort, based on development cohort probabilities. A 95 % confidence interval for the AUC will be calculated using the method of DeLong, and discrimination will also be assessed graphically using ROC curves. Risk stratification will be evaluated by calculating sensitivity, specificity, positive and negative predictive values, and positive and negative likelihood ratios at various threshold levels, including the previously identified 6.4 % probability cut-off. McKelvey and Zavoina pseudo-*R*^2^ will be used to assess the model’s explanatory power and goodness of fit.

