## Conclusion

This protocol outlines a pre-specified and transparent plan for external validation of the Pre-ECPR score using data from the Prague OHCA-trial, a high-quality randomized clinical trial. The analysis will adhere to state-of-the-art methodological standards for external validation and be reported in accordance with the TRIPOD + AI guidelines. The findings will determine whether the predictive performance demonstrated in internal validation is preserved in an external validation cohort, indicating the potential for broader clinical applicability.

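### The statement that no score variable guided ECPR decisions conflicts with Table 1 on arrest time and, indirectly, on age; separately, the observed AUC has no case-mix-adjusted reference

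*Protocol article*

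**What the plan says.** The disputed sentence is in Predictor assessment. It opens with all the score variables and continues "but none was used for decision making regarding ECPR during the study". The next sentence names age and total cardiac arrest time among those variables. The Prediction model section confirms both as predictors and measures arrest time from onset to ECMO flow.

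Table 1 has two blocks. The entry block requires "Age ≥18 and ≤65 years"; a footnote adds that age was estimated at the scene and that "patients later found to be older than 65 years were retained in the study". The second block is headed "Criteria for initiation of ECLS in the invasive strategy group of the Prague OHCA trial". It includes "Admission to cathlab not later than 60 min after the collapse/initial call to emergency medical service" and "Consensus of cardiac center team members on extracorporeal life support initiation", and it excludes patients with apparent death or unrecoverable organ injury. The article does not define how the last two conditions were judged.

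On interpretation, Statistical analysis plans predictor and outcome comparisons between cohorts, a cohort-membership c-statistic, a comparison of predicted-probability distributions with plots, calibration measures, and an AUC with a DeLong interval. It permits refitting where discrimination is poor. The Conclusion states: "The findings will determine whether the predictive performance demonstrated in internal validation is preserved in an external validation cohort".

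**The concern.** A reader who takes the sentence in Predictor assessment at face value will believe that the 92 patients were not selected on anything in the score. That matters because an AUC depends on how widely the predictors vary in the cohort, as well as on whether the coefficients are right. Selecting on a predictor narrows its spread and can lower the AUC of a model that is still correct.

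The second issue is what the observed AUC will be read against. The only internal discrimination figure given is 0.79 (95% CI 0.67 to 0.88), from a development population that covered in-hospital and out-of-hospital arrests. The validation cohort is out-of-hospital only. Without an expected AUC for this case mix, a correct score could be described as not preserved, or a degraded one as preserved. Refitting could also follow, re-estimating the ten non-intercept coefficients in Table 2 from 20 events.

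**Working it through.** **1. The passages side by side.**

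| Variable | Role in the score | Table 1 | Fit with the disputed sentence |
|---|---|---|---|
| Total arrest time | Predictor, onset to ECMO flow | 60-minute limit to the catheterization laboratory, an ECLS initiation criterion, invasive group | Direct contradiction: the limited interval is part of the predictor |
| Age | Predictor | Trial entry criterion, estimated on scene, older patients kept | Indirect: it shaped who could reach ECPR but is not listed as an initiation criterion |
| Pupils, end-tidal CO2, rSO2, pH, initial rhythm | Predictors | No criterion named | No contradiction shown |
| Signs of life | Predictor: spontaneous movement or breathing | Entry requires unconsciousness, defined by lack of response to voice or pain, which is a different variable | No contradiction shown |
| Team consensus; apparent death or organ injury | Not predictors | Listed, undefined | Cannot be decided from the article |

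The initiation block is headed for the invasive group. By Fig. 1 that arm supplies 82 of the 92 patients; the other 10 crossed over.

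**2. The plan's own AUC precision.** Inputs from Sample size: 92 patients, 20 events (so 72 non-events), AUC 0.80. Hanley-McNeil variance:

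- Q1 = 0.80/1.20 = 0.6667; Q2 = 2 × 0.64/1.80 = 0.7111
- Var = [0.16 + 19 × (0.6667 − 0.64) + 71 × (0.7111 − 0.64)]/(20 × 72) = 5.716/1440 = 0.00397
- SE = 0.0630; half-width = 1.96 × 0.0630 = 0.123

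Newcombe's standard error gives 0.110. The stated figure of about 0.12 reproduces.

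**3. How much linear-predictor spread the two limits could remove** (full-model coefficients, Table 2).

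- Age 18 to 65: 1.593 × ln(67/20) = 1.93
- Age 65 to 80: 1.593 × ln(20/5) = 2.21
- Arrest time 30 to 60 min: 0.304 × ln 2 = 0.21; 60 to 120 min: also 0.21

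An age cap can remove material spread. A time limit removes little.

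**4. Effect on the AUC of an exactly correct model.** The full-model linear predictor was simulated with outcomes taken to follow it exactly. The AUC was then compared with and without age ≤65 and total arrest time ≤75 min, the latter standing in for 60 minutes to the laboratory. The article gives no predictor distributions, so all of these are assumptions:

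- predictors independent;
- age normal, mean 55 to 60, SD 12 to 15;
- arrest time log-normal, median 60 min, log-SD 0.4;
- immediate ACLS 40%, PEA/asystole 5 to 20%, dilated pupils 5 to 15%;
- signs of life absent 50%, sedated 20%, present 30%;
- end-tidal CO2 median 3 kPa, rSO2 mean 40 (SD 14), pH mean 6.98 (SD 0.17).

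| Age mean/SD; PEA; pupils | No limit | Age ≤65 | Time ≤75 | Both |
|---|---|---|---|---|
| 55/12; 20%; 15% | 0.855 | 0.846 | 0.855 | 0.846 |
| 55/15; 20%; 15% | 0.862 | 0.848 | 0.862 | 0.849 |
| 58/15; 10%; 10% | 0.835 | 0.811 | 0.835 | 0.811 |
| 60/15; 5%; 5% | 0.815 | 0.782 | 0.815 | 0.782 |

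Across the twelve settings run, the age limit costs about 0.01 to 0.03 and the time limit about 0.001. The simulation isolates these two limits. It does not model the move from a mixed to an out-of-hospital population.

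**The case against.** The strongest reply is that only one sentence is at fault. Any case-mix difference comes from the selection in Table 1, however Predictor assessment is worded. A reader might infer that the misstatement invalidates a comparison of the Prague AUC with 0.79. No such test, margin or success rule is planned, and the Conclusion's sentence covers performance in general.

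A reader might also infer that the planned tools cannot tell selection from wrong coefficients. That is too strong. If the coefficients are right, the expected calibration slope stays at 1 when selection on the predictors narrows their spread, so a low AUC with a slope near 1 points to case mix. The plots of predicted probabilities show spread even though Welch's test compares means. This stands, with one limit: the article's own half-width for the slope is 0.7, so a slope of 1 would carry an interval of roughly 0.3 to 1.7.

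A third tempting inference is a large AUC shift. Assumed out-of-hospital mixes under a correct model can give an AUC anywhere from 0.75 to 0.88, but only by varying pupils, rhythm and signs of life, which Table 1 does not restrict. To say that team consensus drew on those findings would be conjecture.

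Finally, the article says of the membership c-statistic "where a high c-statistic indicates substantial differences between cohorts and a low c-statistic suggests strong similarity". If computed in-sample, its value for identical cohorts would exceed 0.5. The article does not say how it is computed, and such detail may sit in a fuller plan.

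The Discussion already limits the validation to out-of-hospital arrest, and refitting is optional. These points reduce the severity but do not remove the contradiction or supply a reference value.

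**Conclusion.** The statement in Predictor assessment is wrong as written. The conflict is direct for arrest time in the invasive group and indirect for age. For the other score variables the article shows no conflict, but the two undefined conditions leave the question open.

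The likely numerical effect of the listed limits is small: about 0.01 to 0.03 in AUC, a quarter or less of the 0.12 half-width (0.03/0.12 = 0.25). This rests on assumed, independent predictor distributions and on the published model being exactly true.

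The remaining analytic point is one of interpretation. The plan describes case mix and assesses calibration, but it does not connect either to the conclusion about preserved performance or to the decision to refit for poor discrimination. A case-mix-adjusted reference would be a useful addition; its absence is not an error that undermines the validation. Overall severity is minor to moderate.

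**What to change.** 1. **Reconcile Predictor assessment with Table 1.** Limit the statement to the variables for which it is true, say that age and time shaped who received ECPR, and state whether team consensus or the exclusion for death or organ injury drew on any score variable.

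2. **Pre-specify the model-based AUC.** With predicted probabilities p_i in the 92 patients, it is the sum over pairs i ≠ j of p_i(1 − p_j) × [1 if p_i > p_j, ½ if equal], divided by the sum over the same pairs of p_i(1 − p_j). It needs no outcomes, so it fits the blinded phase described under Blinding.

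3. **Report the mean and SD of the linear predictor in both cohorts**, beside the planned distribution plots.

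4. **Tie interpretation to these results.** Read the observed AUC, and any decision to refit, against the model-based AUC together with the calibration slope, not against 0.79 alone.

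Optimism correction of the membership c-statistic is optional.

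The cost is a wording correction and a few lines of code on existing data, fixed before outcomes are unblinded. The downside is a less simple headline than observed AUC against 0.79. The comparison with the model-based AUC will also still carry the observed AUC's half-width of about 0.12.

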### Sample size

With 92 participants and 20 events of favorable neurological outcome, corresponding to an event rate of 22 %, the study is expected to yield the following precision estimates under the assumption of a ROC AUC of 0.80: a 95 % confidence interval halfwidth of approximately 0.12 for the AUC, 0.34 for the observed-to-expected (O:E) event ratio, and 0.7 for the calibration slope.^21^ Calculations were performed using the pmvalsampsize package (version 0.1.0) in R (version 4.2.3).

### Statistical analysis

Model performance will be evaluated in line with established methodological frameworks for external validation of prediction models by Debray et al.^14^

The relatedness of the development and validation cohorts will be evaluated by comparing predictor and outcome frequencies between cohorts, using percentages for categorical variables and means with standard deviations or medians and interquartile ranges for continuous variables, as appropriate. Formal comparisons will be conducted using Pearson’s chi-square test for categorical variables and Welch’s *t*-test or the Mann–Whitney *U* test for continuous variables, depending on data distribution. In addition, c-statistics (AUCs) from logistic regression models predicting cohort membership will be calculated, where a high c-statistic indicates substantial differences between cohorts and a low c-statistic suggests strong similarity. Differences in the distribution of predicted probabilities between cohorts will also be assessed, visualized using box- and scatterplots, and formally tested using Welch’s *t*-test.

Assessment of prediction model performance on the validation cohort will be performed through calibration, discrimination, risk stratification, and model fit statistics. Calibration will be evaluated using calibration-in-the-large, calibration slope, and calibration plots. Calibration-in-the-large assesses whether the predicted probabilities on average are too low, too high, or appropriate. The calibration slope evaluates underfitting or overfitting, that is, whether the predicted probabilities are too close to the mean (underfitting) or too extreme (overfitting), or whether they are adequate. Calibration plots provide a visual presentation of the agreement between observed and predicted event rates. Discrimination ability will be quantified using the ROC AUC and Tjur's discrimination index for the validation cohort, based on development cohort probabilities. A 95 % confidence interval for the AUC will be calculated using the method of DeLong, and discrimination will also be assessed graphically using ROC curves. Risk stratification will be evaluated by calculating sensitivity, specificity, positive and negative predictive values, and positive and negative likelihood ratios at various threshold levels, including the previously identified 6.4 % probability cut-off. McKelvey and Zavoina pseudo-*R*^2^ will be used to assess the model’s explanatory power and goodness of fit.

If the original model demonstrates suboptimal performance or a significant lack of fit in the validation cohort, recalibration will be performed by updating the model intercept and/or calibration slope to align predicted probabilities with observed outcomes. If miscalibration persists or there is evidence of poor discrimination, model refitting may be undertaken, involving re-estimation of model coefficients using the validation data. The performance of the recalibrated or refitted model will then be evaluated through internal cross-validation within the validation cohort to assess the stability and generalizability of calibration estimates.

The Pre-ECPR score is based on a multivariable logistic regression model incorporating eight predictors. To calculate the individual Pre-ECPR score probabilities in the validation cohort, the full model will be used when all data are present, Table 2. Alternative model equations for cases in which arterial pH or INVOS rSO_2_ is missing are available, and for other missing-data patterns further model equations (2*^k^* submodels) will be derived in the development cohort.^22^ Multiple imputation will be used to compute the c-statistics for cohort membership.

Statistical analyses will be conducted using R software (version 4.4.3 or later; R Foundation for Statistical Computing, Vienna, Austria), and results will be reported in accordance with the TRIPOD + AI guidelines.^16^

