### Blinding

The probability of a favorable outcome will be calculated for each individual in the validation cohort while blinded to outcome data. Similarly, comparisons between the model development cohort and validation cohort will be performed blinded to the outcome. Thereafter, outcomes will be unblinded to enable full model performance evaluation and subsequent analyses.

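### McKelvey–Zavoina pseudo-R² cannot show how well the original score fits the validation cohort, whichever linear predictor it is computed on

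*Protocol article*

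**What the plan says.** The Statistical analysis section of the protocol article sets out four groups of performance measures: "Assessment of prediction model performance on the validation cohort will be performed through calibration, discrimination, risk stratification, and model fit statistics". For the last group it names one statistic, McKelvey–Zavoina pseudo-R², and gives its purpose as the model's "explanatory power and goodness of fit".

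Three other statements bear on how it would be computed:

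- Blinding: "The probability of a favorable outcome will be calculated for each individual in the validation cohort while blinded to outcome data".
- Statistical analysis, on the source of the predictions: "the full model will be used when all data are present". This refers to the printed Table 2 coefficients. Other missing-data patterns use equations derived in the development cohort.
- Statistical analysis, on AUC and Tjur's index: these are "based on development cohort probabilities". The McKelvey–Zavoina sentence comes later and has no such qualifier.

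The same section plans calibration-in-the-large, calibration slope, calibration plots, AUC with a DeLong interval, Tjur's index and threshold-based accuracy measures. It then makes model updating conditional on poor performance or lack of fit, without tying any statistic or cut-off to that condition.

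**The concern.** In a model fitted to the data at hand, McKelvey–Zavoina R² depends on the outcomes through the estimated coefficients. In an external validation the coefficients are given in advance. The statistic then measures only how widely the predictions are spread, and it could be computed in full before unblinding. A number available before any outcome is known cannot measure agreement with outcomes.

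The direction of the error also matters. The plan itself describes overfitting as predictions that are too extreme. More extreme predictions mean a larger variance of the LP and hence a higher pseudo-R². A reader who sees a high value labelled as goodness of fit could take it as support for the score when it partly reflects overfitting.

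**Working it through.** **Inputs**

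- Sample size section: "With 92 participants and 20 events of favorable neurological outcome", so the event rate is 20/92 = 0.217.
- Sample size section: precision is worked out "under the assumption of a ROC AUC of 0.80".
- Table 2: the frozen coefficients.
- Assumption, not in the documents: the LP is normally distributed. Solving for event rate 0.217 and AUC 0.80 gives mean −1.70 and SD 1.35.

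The plan states no McKelvey–Zavoina value, so there is no figure to reproduce.

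**Reading A: frozen LP**

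For a logit model R²_MZ = Var(LP)/(Var(LP) + π²/3), with π²/3 = 3.29. No outcome enters.

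If the true calibration slope is b, the frozen LP is the true LP stretched by 1/b, with SD 1.35/b. AUC stays at 0.80 throughout.

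- b = 1.3: SD 1.04, variance 1.08, R²_MZ = 1.08/4.37 = 0.25
- b = 1.0: SD 1.35, variance 1.82, R²_MZ = 1.82/5.11 = 0.36
- b = 0.7: SD 1.93, variance 3.72, R²_MZ = 3.72/7.01 = 0.53
- b = 0.5: SD 2.70, variance 7.29, R²_MZ = 7.29/10.58 = 0.69
- b = 0.3: SD 4.50, variance 20.2, R²_MZ = 20.2/23.5 = 0.86

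The more overfitted the score, the higher the value.

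**Reading B: LP recalibrated to the validation outcomes**

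Logistic recalibration multiplies the LP by the estimated slope. At population level the variance becomes b² × (1.35/b)² = 1.82 for every b, so R²_MZ = 0.36 throughout. Outcomes are used, but the recalibration removes the misfit before the statistic is taken.

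**Simulation, N = 92, 1,500 replicates per setting (means)**

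| True slope | MZ, frozen | MZ, recalibrated | AUC | Tjur | Likelihood-based R², frozen | Brier, frozen |
|---|---|---|---|---|---|---|
| 1.0 | 0.35 | 0.37 | 0.80 | 0.22 | 0.27 | 0.134 |
| 0.7 | 0.53 | 0.37 | 0.80 | 0.29 | 0.22 | 0.139 |
| 0.5 | 0.68 | 0.38 | 0.80 | 0.36 | 0.02 | 0.158 |
| 0.3 | 0.86 | 0.37 | 0.80 | 0.41 | −1.11 | 0.206 |

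The likelihood-based R² has the Nagelkerke form, [1 − exp(2(ℓ₀ − ℓ)/N)]/[1 − exp(2ℓ₀/N)]. Here ℓ is the validation log-likelihood of the frozen probabilities and ℓ₀ that of the observed event rate.

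Two extreme checks:

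- Outcomes randomly permuted (AUC 0.50): frozen MZ stays at 0.35 for the slope-1.0 score and 0.68 for the slope-0.5 score. Recalibrated MZ falls to 0.02.
- Score that ranks patients the wrong way round (AUC 0.20): frozen MZ 0.35, recalibrated MZ 0.37.

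**Dependence on case mix**

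Table 2 coefficients were applied to assumed predictor distributions, none of which are in the documents:

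- age mean 57 (SD 10) years
- arrest time median 60 min (log SD 0.25)
- signs of life absent / sedated / present 60/20/20%
- end-tidal CO₂ median 3.3 kPa (log SD 0.4)
- rSO₂ mean 35 (SD 12)
- pH mean 6.95 (SD 0.17)

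VT/VF was varied from 60% to 100% and pupils ≥6 mm from 0% to 30%. Var(LP) then runs from 1.10 to 7.27 and frozen MZ from 0.25 to 0.69, with no outcome data. The range is driven largely by the coefficients −4.000 (PEA/asystole) and −3.916 (dilated pupils).

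**The case against.** The strongest reply is that the article does not say which LP enters the statistic. The statement about development probabilities covers only AUC and Tjur's index. The measure is ordinarily taken from a fitted model, and the planned calibration slope already requires one. This stands. A reader might infer that the statistic certainly uses no outcomes and certainly rewards overfitting, but both statements depend on the frozen reading, which is the natural one and is not spelled out. What holds under both readings is that the statistic cannot show misfit of the original score.

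A second reply is that overfitting is covered elsewhere, and this also stands. A reader might infer that the validation would miss an overfitted score. The plan does not support that, because it assigns overfitting to the calibration slope and adds calibration-in-the-large and calibration plots. AUC and Tjur's index use outcomes too and would expose a loss of discrimination. They are less help against overfitting alone: in the table AUC does not move and Tjur's index rises. The slope will be imprecise, since the plan expects a half-width of 0.7. A second outcome-based summary is therefore useful, though its absence leaves no gap in coverage.

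A third reply is that nothing depends on the statistic. A reader might infer that it could block or trigger recalibration, but the article attaches no threshold or rule to it.

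**Conclusion.** The point holds: the statistic named for goodness of fit cannot show the fit of the original score. On the frozen LP it goes the wrong way, from about 0.36 at slope 1.0 to about 0.69 at slope 0.5. On a recalibrated LP it stays near 0.37 whatever the miscalibration. The sizes rest on a normal LP calibrated to AUC 0.80 and 20 events in 92. The direction follows from the formula and does not depend on that assumption.

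Severity is moderate to minor. No planned primary performance estimate, confidence interval or stated rule changes, and the other planned measures can reveal misfit. The harm is one reported figure whose label invites a wrong reading.

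**What to change.** Replace McKelvey–Zavoina R² with an overall measure that sets the frozen probabilities against the observed outcomes. This can be the Brier and scaled Brier score, or a likelihood-based R² from the validation log-likelihood with coefficients held fixed, in either case with a bootstrap 95% CI. The table shows that these worsen as overfitting grows.

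If McKelvey–Zavoina is kept, state whether the LP is frozen or recalibrated and describe the result as spread of predictions (case mix), not goodness of fit. It could then sit with the comparison of the two cohorts.

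The change needs a reworded sentence, a few lines of code and no new data. The price is that the reported value may look less favourable; a likelihood-based R² can be negative.

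### The optional refit on the validation cohort alone would rest on 2 events per coefficient and give an overfitted new model; planned updating should stop at intercept and slope

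*Protocol article*

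**What the plan says.** The Statistical analysis section of the protocol article sets out a sequence. The published score is first assessed unchanged for calibration, discrimination, risk stratification and fit. Under Blinding, the individual probabilities are computed before outcomes are revealed. If performance is judged suboptimal or fit significantly lacking, the intercept, the calibration slope or both are updated. If miscalibration remains, or discrimination appears poor, "model refitting may be undertaken, involving re-estimation of model coefficients using the validation data". The updated model is then to be "evaluated through internal cross-validation within the validation cohort", with the stated aim of judging the stability and generalizability of its calibration.

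The article gives no numerical trigger for the refit, no limit on the number of coefficients and no penalty or shrinkage.

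The Sample size section starts from "With 92 participants and 20 events of favorable neurological outcome" and reports the expected precision "under the assumption of a ROC AUC of 0.80": a "confidence interval halfwidth of approximately 0.12 for the AUC", "0.34 for the observed-to-expected (O:E) event ratio" and "0.7 for the calibration slope". In the Discussion, the authors concede that this size restricts what can be detected about calibration and discrimination. They do not connect that limit to the refit.

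**The concern.** A cohort of this size is large enough for a rough check of a fixed score. It is far too small to estimate that score's coefficients afresh. If the refit branch is taken, the product is a new model with unstable coefficients and predictions that are too extreme. That matters here because the score is meant to deliver a probability and is read against a 6.4 % cut-off.

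The route into the branch is also weak. Updating intercept and slope cannot improve the AUC. Poor discrimination, which this cohort can only estimate imprecisely, therefore leads straight to the refit option with no lesser remedy before it.

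**Working it through.** **1. The plan's own figures.** Inputs from Sample size: N = 92, 20 events, 72 non-events, AUC 0.80.
- Event rate: 20/92 = 21.7 %, which agrees with "corresponding to an event rate of 22" per cent.
- AUC half-width (Hanley–McNeil): Q1 = 0.8/1.2 = 0.6667 and Q2 = 2(0.64)/1.8 = 0.7111. Variance = [0.16 + 19(0.6667 − 0.64) + 71(0.7111 − 0.64)]/(20 × 72) = 5.716/1440 = 0.00397. SE = 0.0630 and 1.96 × SE = 0.123. The Newcombe form gives 0.110. The stated value of about 0.12 reproduces.
- O:E half-width: 0.342 from 1.96·√Σp(1−p)/20 with a case mix giving AUC 0.80, which matches 0.34. The closed form on the log scale gives 0.39 to 0.40.
- Slope half-width: 0.53 with a normal or binormal linear predictor, up to 0.66 with a narrower spread. The stated 0.7 is not exactly reproduced, but the article does not give the linear-predictor distribution, so nothing is held against it.

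**2. Events per coefficient (Table 2, full model).** Age 1, rhythm 2, arrest time 1, signs of life 2, pupils 1, end-tidal CO₂ 1, rSO₂ 1, pH 1 = 10 slope coefficients plus an intercept. 20/10 = 2. Updating intercept and slope uses 2 parameters: 20/2 = 10.

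**3. Size needed for a 10-coefficient model.** n = P / [(S − 1)·ln(1 − R²/S)], with P = 10 and target shrinkage S = 0.9. R² is the Cox–Snell value implied by the AUC at an event rate of 0.217.

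| AUC | R² | n for S = 0.9 | events | expected S at n = 92 |
|---|---|---|---|---|
| 0.75 | 0.133 | 626 | 136 | 0.58 |
| 0.80 | 0.191 | 418 | 91 | 0.67 |
| 0.85 | 0.263 | 289 | 63 | 0.75 |

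For AUC 0.80: 0.1913/0.9 = 0.2126; ln(1 − 0.2126) = −0.2390; 10/(0.1 × 0.2390) ≈ 418. The last column solves the same formula for S at n = 92. The 20 available events are 20/91 = 22 % of the number needed at AUC 0.80.

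**4. Separation.** The Table 2 coefficients for PEA/asystole (−4.000) and dilated pupils (−3.916) are odds ratios of exp(−4.000) = 0.018 and exp(−3.916) = 0.020. Few or no events are expected in those groups. A group with no events has no finite maximum-likelihood coefficient.

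**5. Simulated refits.** 400 cohorts per scenario, each of 92 patients with exactly 20 events; unpenalised 10-coefficient refit. Assumptions not in the documents: age mean 56 (SD 10), arrest time median 60 min, end-tidal CO₂ 3.5 kPa (SD 1.5), rSO₂ 40 (SD 14), pH 6.95 (SD 0.17), direct ACLS 10–25 %, PEA/asystole 10–25 %, dilated pupils 10–25 %, sedation 30 %, movement 20 %, no missing data.

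| Truth | Frozen AUC | Refit AUC, new patients | Refit ranks worse | No finite solution | Median refit slope, new patients |
|---|---|---|---|---|---|
| Table 2 true, base mix | 0.87 | 0.83 | 100 % | 91 % | 0.21 |
| Table 2 true, PEA/asystole and dilated pupils 10 % each | 0.80 | 0.75 | 100 % | 99 % | 0.30 |
| Table 2 true, direct ACLS 25 % | 0.87 | 0.83 | 100 % | 93 % | 0.20 |
| Two large negative effects cut to 30 % | 0.73 | 0.71 | 79 % | 18 % | 0.44 |
| Moderate misfit | 0.80 | 0.78 | 78 % | 58 % | 0.15 |
| Strong misfit | 0.64 | 0.76 | 1 % | 9 % | 0.49 |

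Where no finite solution exists, the fitted values depend on where the algorithm stops, so the slopes in rows with much separation are rough. The rows with 18 % and 9 % separation depend least on this, and their slopes are still only 0.44 and 0.49.

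**6. The trigger.** Recalibration replaces LP by a + b·LP. For b > 0 the ranking, and so the AUC, does not change. At the planned precision, an AUC of 0.80 carries an interval of 0.80 ± 0.12, that is 0.68 to 0.92.

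**7. The check on the refit.** With five folds (assumed; the article gives that number only for the development study), each training set has about 16 events, or 1.6 per coefficient, and each test fold about 4. This is internal validation of a new model. The Discussion itself says that internal validation does not suffice to establish performance in other settings.

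**The case against.** The strongest reply is that the main result is safe, and it is. The frozen score is evaluated first, on probabilities computed blind to outcome. A reader might infer that the whole exercise becomes redevelopment or that a refit would supersede the published score. The text supports neither: refitting is optional, conditional and last, and the Discussion requires further validation before clinical use.

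Other parts of the reply also stand:
- The article does not say that all 10 coefficients would be re-estimated or that estimation would be unpenalised. A statistical analysis plan that is not shown may settle this. As written, however, nothing restricts the option.
- The plan prescribes cross-validated performance, so it cannot be said to report apparent performance. Preferring the bootstrap to cross-validation is a matter of taste.
- It is tempting to say that miscalibration cannot persist after recalibration. With both parameters updated, calibration-in-the-large and slope are ideal in the same data by construction. A calibration plot can still show curvature, and an intercept-only update leaves slope error.
- It is tempting to call the refit always non-estimable or worse. Under strong misfit, where the trigger is best justified, it ranked patients better (0.76 against 0.64) and failed to be estimable in only 9 %.
- No AUC cut-off is stated, so any probability of a false trigger would rest on a cut-off chosen by the reader.

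The reply does not remove the overfitting. The refit's calibration slope was poor in every scenario, including the one that favours it most.

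**Conclusion.** The point holds for the refit branch only. Unrestricted re-estimation on 20 events gives 2 events per coefficient, against about 91 events (63 to 136) for an expected shrinkage of 0.9. The expected shrinkage at 92 patients is about 0.67 (0.58 to 0.75). An unpenalised full refit would be severely overfitted, and internal cross-validation in the same patients cannot support a claim of generalizability.

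The coefficient count, the event count and the rank argument follow from the article. The required sizes rest on the assumed AUC. The simulated slopes (0.15 to 0.49) and separation rates (9 to 99 %) also rest on assumed predictor distributions and unpenalised likelihood; the separation rates in particular should be read as a real risk and not as a forecast. No frozen-score estimate or threshold result changes. The point is worth correcting but does not undermine the validation.

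**What to change.** Limit planned updating to the intercept, then intercept plus slope, always reported second to the frozen score. If coefficients are re-estimated at all, state that this will be penalised (ridge or Firth) and preferably done on pooled development and validation data with a cohort-specific intercept. Label the result an exploratory new model that needs its own external validation, and drop the suggestion that cross-validation within these 92 patients speaks to generalizability.

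The cost is a change of wording. It gives up an unrestricted refit that 20 events cannot support. If the score does fail badly, an exploratory penalised refit remains available.
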